### Randomisation

The randomisation process will be conducted by an independent statistician. Stata Version 12 [34] statistical package will be used for the random allocation of subjects to either the intervention or the control group. To ensure equal allocation (1:1), block randomisation method will be used. A pre-defined randomised list containing ID numbers and their respective treatment allocation will be provided to the Project Coordinator (DP) who will not be involved in taking measurements, data management or statistical analyses. ID numbers will be assigned to participants in consecutive order to avoid selection bias.

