**Methods/Design:**

In a parallel-group randomised trial, 180 people with type 2 diabetes of between 2–10 years duration will be recruited via invitation through the Australian National Diabetes Services Scheme. Participants will undergo baseline assessment, followed by randomisation to either intervention or control condition. Control participants will receive fact sheets containing key information about diabetes self-management. The intervention group will receive the INSPIRED (Individual Support & Resources for Diabetes) Manual and be assigned a Health Coach. The INSPIRED Manual consists of six modules that provide key information about diabetes and disease management using the Whole Person Model. Engagement is facilitated by interactive tasks and contact with a Health Coach over seven weeks – an introductory face-to-face session, and six subsequent contacts by phone following each module. Follow-up assessments occur at 13 weeks (post-intervention) and 26 weeks. Primary outcomes include blood glucose management (HbA_1c_), weight and mood. Secondary outcomes include level of exercise, confidence to manage diabetes, and psychosocial well-being.

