### Participant recruitment

Participants with type 2 diabetes will be recruited, via invitation, through the National Diabetes Services Scheme which is a large support scheme for people with diabetes. Approximately 1,098,780 Australians with diabetes are registered with the National Diabetes Services Scheme, of which 86% have been diagnosed with type 2 diabetes. Approximately 6% include those who reside in Victoria, meet inclusion criteria and have nominated to receive information about research opportunities related to diabetes. These individuals will be invited to participate in the project. This method of recruitment will be supplemented by advertisement online via the Diabetes Australia, Victoria website. People will indicate their interest by contacting the research team by telephone. Inclusion criteria are: 1) having had diagnosed type 2 diabetes for between 2 and 10 years, 2) aged 18 years or over, 3) a Body Mass Index (BMI) between 20 and 40, 4) not currently on insulin, 5) sufficient speech and reading fluency in English to read and understand the INSPIRED Manual (determined using the Single Item Literacy Screener [33]), and 6) able to give informed consent. People will be excluded if they have significant cognitive impairment or other infirmity which would obviously preclude their participation. If eligible and willing to participate, potential participants will be met by a research assistant, when consent forms will be signed and baseline measures taken.

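### Allocation concealment is not assured: the team member who holds the ID-to-treatment list is not barred from screening, enrolment or ID assignment, and consecutive IDs alone do not close that gap

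*Protocol article*

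**What the plan says.** The Randomisation section of the protocol article sets out the mechanism:

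- Generation: "The randomisation process will be conducted by an independent statistician", with 1:1 allocation in blocks.
- Custody of the list: "A pre-defined randomised list containing ID numbers and their respective treatment allocation will be provided to the Project Coordinator".
- Limits on the holder: the coordinator is someone "who will not be involved in taking measurements, data management or statistical analyses".
- Stated protection: "ID numbers will be assigned to participants in consecutive order to avoid selection bias".

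The Participant recruitment section describes entry. First contact is by telephone: "People will indicate their interest by contacting the research team by telephone". Those found eligible and willing then attend a visit, where "potential participants will be met by a research assistant, when consent forms will be signed and baseline measures taken".

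The Methods/Design part of the Abstract gives the order of events: "Participants will undergo baseline assessment, followed by randomisation to either intervention or control condition". The sections Outcomes assessments and Study integrity and quality assurance add that the research assistant who collects data does not know group membership; the latter names the baseline assessment explicitly. It also gives the Project Coordinator the task of monitoring the coaching through recorded sessions.

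**The concern.** Treatment is tied to the ID number and IDs are issued in order. Anyone who can see the list and knows the last ID issued therefore knows the next allocation. The article places that list with someone who works inside the trial, and offers consecutive numbering as the protection against selection bias.

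Consecutive numbering stops someone picking an ID out of turn. It does not stop someone who knows the next allocation from influencing who takes the next ID, or when. If that happened, a caller could be encouraged, deferred or judged unsuitable depending on the arm that came next, and the two groups could differ at entry for reasons other than chance. The between-group comparisons of HbA1c, weight and mood all rest on the groups being comparable at entry.

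**Working it through.** No arithmetic applies, and the article gives no figure to reproduce. The check sets the steps from first contact to allocation side by side and asks, for each, who carries it out and whether that person is kept from the list.

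| Step | Who does it, per the article | Kept from the list? |
|---|---|---|
| Generate the sequence | Independent statistician | Not applicable: produces it |
| Hold the list | Project Coordinator | No: holds it |
| Take the telephone call | Research team, role not named | Not stated |
| Settle eligibility and willingness | Not named; placed before the visit | Not stated |
| Book the baseline visit | Not named | Not stated |
| Consent and baseline measures | Research assistant | Described as uninformed of group |
| Issue the next ID | Not named; moment not stated | Not stated |
| Assessments at 13 and 26 weeks | Research assistant | Described as uninformed of group |

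**Step 1: what the coordinator's exclusions protect.** The three barred tasks are measurement, data management and statistical analysis. All concern how data are obtained, handled and analysed. None is a step at which a person is admitted to the trial or given an ID, so they do not address selection bias.

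**Step 2: what consecutive IDs protect.** Suppose the last ID issued is k. The next entrant receives k+1, and the list shows the treatment for k+1. If the people who screen, book and issue IDs cannot see the list, k+1 tells them nothing about treatment through this route. If any of them can, they know the next arm before the person enters, and keeping strictly to the order does not change that. The safeguard is conditional on a separation of roles that the article does not state.

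**Step 3: what the research assistant protects.** This person takes consent and baseline measures without knowing the group. That covers the visit. The Participant recruitment section, however, makes the visit conditional on the person already being eligible and willing. That judgement therefore comes earlier, on or after the telephone call, and belongs to someone whom the article neither names nor requires to be unaware of the list.

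**Step 4: what the order of baseline and randomisation protects.** Taking baseline first means that the measurements cannot be coloured by a known assignment. With a list made in advance, however, the assignment attached to the next ID already exists before the visit. The order guards against foreknowledge only if the list holder has no influence on who reaches the visit or when.

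**Step 5: how much room for discretion there is.** Diabetes duration, age, BMI, insulin use and the literacy screener are largely objective. Discretion remains in the exclusion for other infirmity, in judging willingness, and in the timing of the visit.

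**The case against.** The strongest reply is that the one role named at the point of entry is the research assistant, who obtains consent, takes baseline measures and does not know the group. Randomisation follows. No sentence says that the Project Coordinator answers calls, screens, books visits or issues IDs; the documented tasks are holding the list and monitoring the coaching. A list holder who is separate from recruitment and reveals each assignment only after baseline could preserve concealment. The article is also a condensed account, and the full protocol may name who does what.

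Much of this stands. A reader might infer from the custody of the list that allocation is unconcealed. The article does not support that: it never places the coordinator in the entry process, and the absence of a bar is not evidence of involvement. Nor does it support criticism of block size, which it does not give.

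What the reply does not remove is the problem in the stated text. The article does more than leave a detail out. It says who receives the list, lists the tasks that this person is kept away from, and gives consecutive numbering as the reason why selection bias is avoided. The listed exclusions address other biases, and the stated reason is insufficient without a further condition. The research assistant's ignorance of group does not reach the telephone step.

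**Conclusion.** The point holds in a limited form: concealment is not assured by the procedure described. The full list goes to an operational team member who is not kept from screening, eligibility decisions, booking or ID assignment, and consecutive numbering does not by itself supply the missing protection. The research assistant's role and the baseline-first order lower the risk without removing it.

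This rests on reading the pre-defined list as handed over whole. The article does not describe release in parts. On that reading, and if the list covers the planned sample, its holder can see the assignments for all 180 planned participants ahead of their entry.

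No size can be put on any resulting bias. The article has no information on how often entry could be influenced or by how much outcomes would shift, so any figure would be invented. This is a weakness in the procedure that is cheap to correct and should be corrected. It is not a demonstration that the comparison is biased.

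**What to change.** Preferred: the independent statistician, who is already engaged, keeps the list. Each allocation is released singly, and only once eligibility, consent and all baseline measures have been logged under the participant's ID. The coordinator then sees only past allocations, which is enough for posting control materials and assigning Health Coaches.

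Minimum: if the coordinator must hold the list, add a statement barring the list holder from telephone screening, eligibility decisions, booking, enrolment and ID assignment. State who issues IDs, and that each allocation is disclosed only after baseline is complete.

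In either case, reword the sentence on consecutive IDs so that the protection is attributed to keeping the list from those who influence entry, with consecutive issue as a supporting rule.

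The preferred option costs one short request and reply per participant and a short delay between baseline and allocation. The minimum option costs a few sentences and a clear division of tasks. Either has to be in place before participants enter, because concealment cannot be restored afterwards for those already allocated.

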### Intervention

Participants randomised to the control group will receive standard information sheets containing key information about diabetes and diabetes self-management. The information sheets primarily include those which are part of an information series from State/Territory organisation of Diabetes Australia. These will be posted to participants from the study headquarters.

Participants randomised to active treatment will be assigned a trained Health Coach, and will be provided with the INSPIRED Manual during an initial face-to-face meeting with their Health Coach. The INSPIRED Manual provides key information about diabetes and management of diabetes, guidance about diet and exercise, and skills training. Issues of emotions (determined, sad, anxious, angry) are acknowledged and addressed in the context of their disease self-management and their relationships with family and health professionals. This is all designed to facilitate self-management. The specific topics covered have been developed through consumer participation and consultation with key clinical experts and stakeholders (see Table 1 for further intervention details). Using the Whole Person Model, the INSPIRED Manual in combination with the support and guidance of a Health Coach, aims to encourage the reader to consider how their body, their thoughts and feelings, and their health behaviors are all interdependent. This combination aims to help people to be aware of their thinking and learn strategies to improve their mood and make lifestyle changes. An accompanying INSPIRED Journal will also be provided to participants, which assists them to keep track of their medical appointments, health goals and to improve communication with their health professionals.

**Table 1 T1:** Overview of the INSPIRED intervention

**INSPIRED manual content**	**Health coach support**
Diabetes information	Providing weekly support and education about:
	▪ General diabetes
	▪ Diabetes complications
	▪ Hypoglycaemia episodes
	▪ Medication
	▪ Diabetes and driving
	▪ Diabetes and alcohol/smoking
	▪ Importance of self-management
Healthy eating	Providing weekly support and education about:
	▪ Barriers to healthy eating
	▪ Tips for healthy eating and snack choices
	▪ Managing food cravings
	▪ Home-grown experiments
	▪ Emotions and eating
	▪ Eating out
	▪ Reading food labels
Becoming more physically active	Providing weekly support and education about:
	▪ Attitudes about different types of physical activity
	▪ Benefits of physical activity
	▪ Keeping track of your steps using your pedometer
	▪ How to be more physically active
	▪ Physical activity and blood glucose levels
Weight management	Providing weekly support and education about:
	▪ Your Body Mass Index
	▪ Losing weight the healthy way
	▪ Weight loss and maintenance tips
	▪ Healthy eating tips for weight loss
Monitoring your diabetes	Providing weekly support and education about:
	▪ Keeping track of your diabetes using your Journal
	▪ Paying attention to your blood glucose levels
Maintaining contact with your doctor and other health professionals	Providing weekly support and education about:
	▪ Choosing a doctor
	▪ The importance of keeping in regular contact with your doctor
	▪ How to get the most from your doctor’s visit
Family and social support	Providing weekly support and education about:
	▪ Carers and helpers
	▪ Staying connected
	▪ Making friends
Dealing with emotions (i.e., worry, anger)	Providing weekly support and education about:
	▪ Negative thoughts
	▪ Managing distress
	▪ Relaxation
	▪ Reducing feelings of tension and worry – problem solving
	▪ Tips to reduce the impact of anger
The Whole Person Model	Providing weekly support and education about:
	▪ The Whole Person Model
	▪ Considering your body, feelings and thoughts when making an Action Plan
	▪ Examining your thinking and talking back unhelpful thoughts
Toolbox for a healthy life	Providing weekly support and education about:
	▪ What to put in your tool box for a healthy life?
	- Things I am going to try
	- Things I am going to think about
	- Other ideas

Participants will receive seven sessions with a Health Coach over a 7 week period as follows:

•One face-to-face session, involving an orientation to the INSPIRED Manual and the Whole Person Model, conducted at the study headquarters.

•Six weekly phone coaching sessions. During these calls the Health Coach will support the participant working through the INSPIRED Manual, answering questions, helping with goal-setting, and discussing the homework exercises.

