### Study integrity and quality assurance

Ethical approval for this study has been obtained from both the Monash Health Human Research Ethics Committee and the Monash University Human Research Ethics Committee. The study design will be guided by the CONSORT statement [45,46]. Each participant will be screened for eligibility and enrolled if eligible and consenting. To ensure consistency and best practice, participant’s height, weight and girth measurements are taken as per recommendations outlined by the World Health Organization [47]. The randomisation process will be conducted by an independent statistician. Assessments at baseline, 13 and 26 weeks will be carried out by a research assistant who will be uninformed of group membership. All Health Coaches who will be delivering the intervention are qualified Diabetes Educators and trained in the Whole Person Model. As well as the initial training, reflective practice support and supervision will be provided to the Health Coaches. The Project Coordinator will monitor the delivery of the intervention via recordings of phone sessions for the first participant of each Health Coach and random subsequent coaching sessions. Constructive feedback will be provided where necessary, and a fidelity checklist completed. Quality of health coaching will also be assured using measures of treatment alliance. No significant risks to participants are anticipated.

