### Sample size justification

Using information from comparative studies, 150 participants are required to detect a between group difference of 0.7% (SD ± 1.5) in HbA_1c_, with 80% power and at an alpha level of 0.05 [48]. Similarly, 150 participants are needed to detect a between group difference in weight of 4.4 kg (SD ± 9.6) with 80% power and at an alpha level of 0.05 [49]. Based on a comparative sample using the DASS [50], at least 116 participants are required to detect a hypothesised reduction of 25% in DASS score (20 to 15, SD ± 9.6). On the basis of this analysis, and assuming a dropout rate of 20% based on prior experience, we estimate that a recruited sample of 180 will be required and be sufficient to give the requisite power.

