### Statistical analyses

Continuous variables will be assessed for their distribution and outliers prior to analyses. Variables will be transformed if distributional/linearity assumptions are violated. We will compare group characteristics using student t-test for continuous variables, Chi-square (χ^2^) or Fisher’s exact test for categorical variables. We will conduct univariable and multivariable linear regression analyses adjusting for appropriate covariates and test for interactions. For dichotomous outcomes, logistic regression analyses will be implemented. All analyses are to be conducted on an intention-to-treat basis (ITT). However, we may conduct a sensitivity analysis using the imputation method chained equations (ICE) if we find a disproportionate level of missing values that are assessed as missing at random (MAR). Stata Version 12 [34] will be used for all statistical analyses.

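### Intervention participants share Health Coaches, but the sample size and the named regression make no allowance for correlation within coach; the effect ranges from negligible to material, depending on values the protocol does not give

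*Protocol article*

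**What the plan says.** Under Intervention, the protocol article says: "Participants randomised to active treatment will be assigned a trained Health Coach". It then says: "Participants will receive seven sessions with a Health Coach over a 7 week period". Controls are sent information sheets: "These will be posted to participants from the study headquarters". No coach is described for them.

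Study integrity and quality assurance speaks of coaches in the plural: "All Health Coaches who will be delivering the intervention are qualified Diabetes Educators and trained in the Whole Person Model". Monitoring uses "recordings of phone sessions for the first participant of each Health Coach and random subsequent coaching sessions". No caseload is stated, but this wording implies that a coach sees more than one participant.

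Sample size justification gives, for each primary outcome, a difference, a standard deviation and a required number. These are 150 for HbA1c, 150 for weight and at least 116 for the DASS, leading to 180 recruited with 20% dropout. It mentions no ICC, design effect or coach caseload.

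Statistical analyses states: "We will conduct univariable and multivariable linear regression analyses", with covariate adjustment. It names no coach effect and no clustered standard error.

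**The concern.** Randomisation is individual, but the treatment in one arm comes from a limited set of people, each serving several participants. This is a partially nested design: clusters in the intervention arm, none in the control arm. If some coaches obtain better results than others, outcomes under the same coach are correlated, and the intervention arm carries less information than its head count suggests.

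A calculation or model that treats all participants as independent would then give confidence intervals that are too narrow and overstate power. All three primary outcomes are exposed. The protocol article also asserts that 180 is sufficient for the requisite power, and the sample has no spare margin for weight.

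**Working it through.** **Inputs from Sample size justification:** HbA1c difference 0.7, SD 1.5; weight difference 4.4 kg, SD 9.6; DASS difference 20 − 15 = 5, SD 9.6; 80% power; alpha 0.05 (taken as two-sided, which reproduces the stated numbers; one-sided does not). Allocation is 1:1 (Randomisation).

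**Step 1: reproduce the stated numbers without clustering.** n per arm = 2 × [(1.96 + 0.84) × SD / difference]², rounded up.

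- HbA1c: 73 per arm, 146 in total (stated 150).
- Weight: 75 per arm, 150 in total (stated 150).
- DASS: 58 per arm, 116 in total (stated at least 116).

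Two match exactly and HbA1c is within 3%. No allowance for coach clustering is built in.

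**Step 2: number analysed.** 180 × (1 − 0.20) = 144, or 72 per arm. Power with independent observations is Φ(difference / SE − 1.96), where SE = SD × √(2/72).

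- HbA1c: SE 0.25, ratio 2.80, power 80.0%.
- Weight: SE 1.60, ratio 2.75, power 78.5%.
- DASS: SE 1.60, ratio 3.125, power 87.8%.

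Weight is thus slightly under 80% before any clustering. That shortfall comes from the dropout arithmetic and is not part of this point.

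**Step 3: add clustering in the intervention arm only.** With k coaches, caseload m = 72/k and design effect DE = 1 + (m − 1) × ICC. The true SE is SD × √((1 + DE)/72), so true SE / naive SE = √((1 + DE)/2). The actual alpha of the naive test is 2 × [1 − Φ(1.96 × naive SE / true SE)]. Both k and the ICC are assumptions.

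| Assumed | m | DE | True/naive SE | Naive SE too small by | Alpha of naive test | Power HbA1c | Power weight | Power DASS |
|---|---|---|---|---|---|---|---|---|
| ICC 0 | – | 1.00 | 1.000 | 0% | 5.0% | 80.0% | 78.5% | 87.8% |
| 15 coaches, 0.01 | 4.8 | 1.038 | 1.010 | 1% | 5.2% | 79.2% | 77.8% | 87.2% |
| 8 coaches, 0.02 | 9 | 1.16 | 1.039 | 4% | 5.9% | 76.9% | 75.4% | 85.2% |
| 4 coaches, 0.05 | 18 | 1.85 | 1.194 | 16% | 10.1% | 65.0% | 63.4% | 74.5% |

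Worked line for weight, 4 coaches: DE = 1 + 17 × 0.05 = 1.85; true SE = 1.60 × 1.194 = 1.91; 4.4/1.91 = 2.304; Φ(2.304 − 1.96) = 63.4%. The naive SE is 1/1.194 = 0.838 of the true one, hence 16% too small; equivalently, the true SE is 19% larger.

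Power here is that of a test using the correct SE under a normal approximation. Small-sample degrees of freedom would lower it further when coaches are few.

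**Step 4: check by simulation.** A simulation of 20,000 runs at 75 per arm gave a naive type I error of 0.066 for 5 coaches at ICC 0.02 (formula 0.066) and 0.089 for 5 coaches at ICC 0.05 (formula 0.092).

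**The case against.** Several counter-arguments have force.

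**Harm is conditional.** A reader might infer that the standard errors are certainly too small and that type I error certainly exceeds 5% for all three outcomes. The documents do not support that, because they give neither the ICC nor the number of coaches. Coaches are met only after individual randomisation. If the programme does nothing for anyone, and participants are not matched to coaches by prognosis, coaches induce no correlation and the naive test keeps its level. Inflation needs real coach effects that average to zero and inference to a wider population of coaches. For a conclusion confined to the coaches used, treating them as fixed is defensible. This stands, and the verdict carries both conditions.

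**Quality assurance is not evidence of variation.** A reader might infer from the supervision, session recordings, fidelity checklist and alliance measures that the plan expects coaches to differ. The text presents these as means of standardising and assuring delivery, and it describes no coach-level alliance scores. The inference is not supported.

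**A condensed article may leave a coach term to the analysis plan.** This is fair for the model: nothing in Statistical analyses rules out such a term. It does not cover the sample size, which is fixed in this document under independence and declared sufficient.

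**Power may be better than shown.** The figures use unadjusted SDs. All three primary outcomes are also measured at baseline, and adjustment for baseline, if used, could offset a small design effect on power. It would not correct a standard error that ignores the coaches, since coach effects arise after baseline. The DASS also has slack and stays above 80% in the two milder scenarios.

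**Conclusion.** The point holds in conditional form. Coaches are shared in one arm, the stated sample sizes assume independence, and the named regression contains no coach term. If the coach ICC is above zero and the trial is meant to speak beyond its own coaches, the naive standard error is too small and power is lower than the independence calculation shows.

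The size cannot be fixed from the document. Over the assumed range it goes from negligible to a loss of about 15 points of power for weight (78.5% to 63.4%), with the test's level doubled. Weight and HbA1c have no margin to absorb this. The Discussion's aim of wide implementation by Diabetes Educators suggests that the wider population of coaches is the intended target, although the article does not state an inferential target. This should be addressed, with medium confidence in its practical size.

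**What to change.** Record the coach's identity for every intervention participant. Analyse the primary outcomes with a coach random effect in the intervention arm only (each control a cluster of one), arm-specific residual variance and small-sample degrees of freedom. Report the coach ICC for each primary outcome.

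If there are too few coaches to estimate the variance, present this model as a sensitivity analysis beside the stated regression.

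In Sample size justification, state the number of coaches and restate power over an ICC range such as 0 to 0.05. This needs no additional participants.

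The cost is one extra variable and a modest change to the model. The downside is wider intervals if coaches differ, and an imprecise coach variance if there are few of them.
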